### Data Management and Participants’ Safety

The research team will be the sole individuals with knowledge about and access to the names of both the older and young participants. Although certain demographic information, such as age, sex, and racial and ethnic background, may be recorded, the questionnaires will not contain any participant identifiers such as date of birth or address. The preintervention and postintervention questionnaires will also be devoid of participant identifiers. To ensure confidentiality, participant names will be deidentified, with each individual assigned a unique study identifier or number. All data files will be securely stored in encrypted, password-protected folders on laptops provided by UTA. These laptops will also have encryption in accordance with the guidelines set by the UTA Office of Information Technology. Participant privacy will be diligently safeguarded, and records containing names and other identifiable information will be stored separately from the interviews, using password-protected, encrypted files on UTA-issued laptops. The PI (LX) and the UTA institutional review board (IRB) will bear the responsibility of ensuring participant safety and the attainment of the study’s scientific objectives. The research team possesses previous experience in organizing and managing clinical trials, including implementing data safety monitoring measures for interventions.

All the older adults and young adult volunteers will provide informed consent before participating in the study. Potential participants will be informed that refusal to consent to the study or withdrawing from the study will have no effect on the services that they currently receive or might receive through UTA (ie, young adult volunteers) or through MOW or the Area Agency on Aging (ie, older adults). Participants who provide informed consent will be contacted for baseline measurement and then randomized to 1 of the 2 treatment groups. The protocol and consent forms will be approved by the UTA IRB before conducting any study procedures. Student members of the research team will receive training regarding procedures required to obtain informed consent.

Human participants’ risk related to the study is minimal. The study carries potential risks related to the identification of depression or anxiety, as participants may become aware of their symptoms during the intervention sessions. This heightened awareness could lead to the recognition of distressing thoughts. In addition, there is a risk associated with the process of recalling past memories, as it may evoke difficult or emotional experiences for participants. Every effort will be made to minimize risks by closely monitoring the participants’ mood during weekly fidelity treatment checks. In the event that a study participant experiences emotional distress during the study, [name], a registered nurse and gerontological nurse practitioner, along with [name], a licensed clinical social worker, will be responsible for providing the necessary support and counseling to address the participant’s emotional well-being. They will also be available as needed for referral to the resources through the local Area Agency on Aging for the older adults and university services for the young adult volunteers, as needed.

### Ethics Approval

The study was approved by the UTA IRB on March 25, 2021 (2021-0206).

## Results

The study was funded in January 2021. Data collection started in May 2021 and ended in mid-2022. In total, 103 dyads were matched at the beginning of the intervention. Of the 103 dyads, 90 (87.4%) dyads completed the midtest survey and 64 (62.1%) dyads completed the posttest survey. Although a total of 92 dyads were planned to test the effectiveness of the intervention in this proposed study, the post hoc power analyses performed using G*Power 3.1.9 indicated that 64 dyads will yield sufficient power to test the interaction between groups over time (power=0.95), the changes over time (power=0.95), and the differences between the groups (power=0.71). These parameters are based on a small anticipated effect size (*f*=0.22), α=0.05, two-tailed, with measures correlated at r=0.30.

We also collected qualitative interview data for this study with selected dyads in the intervention group (8/27, 30%). Weekly reflection page from UTA student participants, weekly fidelity check forms, final digital story books, and final scrapbooks were also saved for future data analyses. We are currently engaged in data cleaning and analysis for both quantitative and qualitative data. One manuscript has already been published [73], and we anticipate publishing several more manuscripts reporting the results within the next 1-2 years.

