**Results:**

The project was modified to a telephone-based intervention owing to the COVID-19 pandemic. Data collection started in 2020 and ended in 2022. In total, 103 dyads were matched at the beginning of the intervention. Of the 103 dyads, 90 (87.4%) dyads completed the midtest survey and 64 (62.1%) dyads completed the whole intervention and the posttest survey. Although we are still cleaning and finalizing data analyses, the preliminary results from both quantitative and qualitative data showed promising results of this intergenerational reminiscence approach that benefits both the older adults who have cognitive impairments and the young adult participants.

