### Sampling and Recruitment Plan

Power analyses performed using G*Power 3.1.9 indicated that a total of 92 dyads (or 184 participants) are required to address our study objectives using a linear mixed model. This sample size estimate was based on a small effect size *(f*=0.22), a significance level of α=.05, β of .20, anticipated *r* over time of 0.30, and 5% attrition rate based on the findings of Chung [25], for 2-tailed tests.

Participants in this study will be community-dwelling older adults and undergraduate and graduate students (ie, young adult volunteers) enrolled at UTA. The eligibility criteria of the older adult participants include individuals who (1) are aged ≥65 years; (2) have cognitive impairment measured by the Ascertain Dementia 8 (AD8) [41]; (3) have decisional capacity as measured by the University of California, San Diego Brief Assessment of Capacity to Consent (UBACC) [42]; (4) are not participating in any other research protocol currently; and (5) can speak and understand English. The exclusion criteria for older adults are (1) participating in another trial, (2) having health issues that prevent them from participating in the study for 3 months, and (3) inability to commit to being available for the full 10 weeks of the intervention.

The older adult participants will be recruited through Tarrant County Meals On Wheels (MOW), which is a partner agency of the Area Agency on Aging of Tarrant County. Eligibility criteria to enroll in Tarrant County MOW is that a person must be homebound and have no one to help them on a regular basis. The Area Agency on Aging is very committed to expanding services and supports to people with ADRD, as many MOW clients with ADRD are living alone in Tarrant County. Moreover, studies suggest the need for additional research in the area of loneliness among clients using MOW [43]. Participant recruitment will begin with case managers and other MOW staff using their client database system to search for clients with ADRD who meet the study criteria. Next, case managers will contact potential study participants and then ask for permission to share their telephone number with a member of the UTA research team. The principal investigators (PIs) and graduate research assistants (GRAs) will follow-up with all the potential participants provided by MOW.

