### Data Collection Plan

Data will be collected at baseline, midpoint, end of the intervention, and 3 months after the intervention by telephone. A total of 3 GRAs will be trained to collect the data. Training on the assessment battery and interview techniques will be provided by PIs to GRAs. For the quantitative survey, after training, interrater reliability checks will be performed by 1 PI on pilot interviews of team members and participants (3 older adults and 3 college students not included in the final sample size), based on audiotaped interviews. For the qualitative interviews, training related to conducting interviews will be provided to GRAs, such as talking less and listening more, how to build rapport with the respondents, and how to handle unexpected emotions of participants. The GRAs will also pilot-test their qualitative interviewing skills based on role-plays with the research team. GRAs will have weekly supervision meeting with the PIs regarding participant recruitment and follow-up and survey assessments.

Several strategies will be used to track clients during the study and to minimize attrition. At the baseline and at each subsequent interview, participants will be asked to provide the names of 2 people who may know where they are if the researcher has difficulty in contacting them. We will also have the older participants’ MOW case managers as a backup point of contact. We will adopt the strategies of minimizing attrition in longitudinal studies [66], which results in 90% follow-up. These strategies (ie, getting several contacts, getting emails, reminder letters, and thank you letters) have proved to be useful in previous community-based studies conducted by the research team.

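### The Results call power sufficient for all three tests with 64 dyads, but the between-group figure (0.71) is below the planned 0.80, and the figures imply four waves although 64 is the count at the third

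*Protocol article*

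**What the plan says.** The Sampling and Recruitment Plan asks for 92 dyads, using G*Power with f=0.22, "a significance level of α=.05, β of .20", a correlation over time of 0.30 and 5% attrition. A β of .20 is a planned power of 0.80.

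The Results section reports 103 dyads matched, 90 at the midtest and 64 at the posttest; the abstract words the last count as "64 (62.1%) dyads completed the whole intervention and the posttest survey". The Results section acknowledges that 92 dyads were planned. It then states that "64 dyads will yield sufficient power to test the interaction between groups over time (power=0.95"), and lists under the same claim the change over time (0.95) and "the differences between the groups (power=0.71"). The basis is given as follows: "These parameters are based on a small anticipated effect size (*f*=0.22), α=0.05, two-tailed, with measures correlated at r=0.30". The number of repeated measures is not stated.

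Figure 1 and the Study Design section define four waves: baseline (O1), mid-intervention (O2), end of intervention (O3) and 3 months later (O4). The posttest is O3. The article gives no count of dyads with O4 data.

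**The concern.** One adjective covers three tests, and one of the three misses the standard that the plan set for itself. Nothing in the sentence or in the Limitations says so.

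The figures also appear to credit the 64 dyads with more data than the article documents for them. Power in a repeated-measures calculation depends on how many measurements each participant contributes. If the calculation assumed four and the 64 dyads are known to have reached only the third, the printed figures are too favourable for the data described.

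This matters because the sentence is the article's answer to a loss of 39 of 103 dyads (38%) by posttest. Goals 1 to 4 all include an intervention-versus-control hypothesis, and further results papers are announced. Readers of those papers may take from it that every planned comparison was adequately powered.

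**Working it through.** **Inputs.** N=64 dyads (Results); two groups (Study Design); "small anticipated effect size (*f*=0.22"), α=0.05 and "with measures correlated at r=0.30" (Results); planned power 0.80 (Sampling and Recruitment Plan). The number of waves m is not stated, so it is varied. Sphericity (ε=1) is assumed, in line with the single correlation given.

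**Formulas** (repeated-measures ANOVA in the G*Power parameterisation, noncentral F):
- Between groups: λ = f²·N·m / (1 + (m−1)·r), with 1 and N−2 degrees of freedom.
- Time, and group-by-time interaction with two groups: λ = f²·N·m / (1−r), with m−1 and (N−2)(m−1) degrees of freedom.

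Here f² = 0.22² = 0.0484.

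**Step 1: reproduce the stated figures (m=4).** f²·N·m = 0.0484 × 64 × 4 = 12.390.
- Between: λ = 12.390/1.9 = 6.52, df 1 and 62, power 0.710.
- Time and interaction: λ = 12.390/0.7 = 17.70, df 3 and 186, power 0.952.

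These match the stated 0.71, 0.95 and 0.95.

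**Step 2: the same 64 dyads with the three waves they are documented to have reached (m=3).** f²·N·m = 0.0484 × 64 × 3 = 9.293.
- Between: λ = 9.293/1.6 = 5.81, df 1 and 62, power 0.660.
- Time and interaction: λ = 9.293/0.7 = 13.28, df 2 and 124, power 0.907.

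**Step 3: two waves (m=2), to complete the comparison.** f²·N·m = 6.195.
- Between: λ = 6.195/1.3 = 4.77, power 0.575.
- Time and interaction: λ = 6.195/0.7 = 8.85, power 0.834.

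| Waves per dyad | Between groups | Time | Interaction |
|---|---|---|---|
| Stated | 0.71 | 0.95 | 0.95 |
| 4 | 0.710 | 0.952 | 0.952 |
| 3 | 0.660 | 0.907 | 0.907 |
| 2 | 0.575 | 0.834 | 0.834 |

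Only m=4 returns the stated figures.

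**Step 4: compare with the target.** Between-group power is below 0.80 in every row: short by 0.09 with four waves and by 0.14 with three. Time and interaction are above 0.80 in every row.

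**Step 5: allow for partial data.** The planned analysis is a linear mixed model, which also uses dyads that dropped out. Assume monotone, ignorable dropout, so that 64 dyads have three waves, 26 (90−64) have two and 13 (103−90) have one. Assume also a group difference that is constant over these waves, and ignore O4. The information terms are 64×3/1.6 = 120, 26×2/1.3 = 40 and 13×1/1 = 13, in total 173. Then λ = 0.0484 × 173 = 8.37, df 1 and 101, power about 0.82. This is not the calculation in the article, which speaks of 64 dyads, but it shows that 0.66 is a complete-case figure.

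**The case against.** The strongest reply is that nothing is hidden and most of the sentence is right. The 0.71 is printed next to the planned 92 and the assumptions, and the 103/90/64 counts come just before. The interaction figure is arithmetically correct for four waves, and the time and interaction tests stay adequate with three. The Statistical Analysis section uses the interaction to detect different patterns of change, so the between-group main effect may be the less important test. All of this stands. It is why the correction is confined to the between-group test.

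It is also fair that four waves is the planned design, that the wave count is inferred from the match rather than stated, and that a missing O4 count does not prove that the 64 lacked O4 data. The point is that the article does not show that they had it, and the figures need it.

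Finally, the planned mixed model uses partial data and could reach about 0.82 between groups. That holds only if dropout is ignorable and the group difference is constant over the waves used, baseline included. The Data Collection Plan itself warns of systematic dropout, and the article does not make this argument.

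Several stronger readings are tempting but not supported:
- **That the planning calculation used three waves and so a different design.** The wave count is not stated there. With four waves, 92 dyads give 0.86 between groups, and the 87 left after 5% attrition (92 × 0.95 = 87.4) give 0.84. Four waves is therefore compatible with the 0.80 target.
- **That the between-group test is known to have set the sample size.** The section names no test.
- **That the article calls a null result informative.** It does not say so; that would be the reader's own inference.
- **That the planned 5% attrition, or the retention strategies described with "which results in 90% follow-up", should be replaced by the observed 38%.** The first two are prospective, and the actual loss is already disclosed.

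**Conclusion.** The statement is wrong as written, in a limited way. By the article's own figure, between-group power with 64 dyads is 0.71 against a planned 0.80. That part needs no assumption. The stated figures correspond to four complete waves, while 64 is the third-wave count; with three complete waves the figures are about 0.66 between groups and 0.91 for time and interaction. That part rests on the G*Power repeated-measures formulas with two groups, f=0.22, r=0.30 and ε=1, and on inferring the wave count from the match.

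The whole power claim should not be read as false: under the same assumptions, sufficiency holds for the time and interaction tests with either three or four waves. Nor should 0.66 be read as the power of the planned mixed model.

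**What to change.** In the Results section:
1. Restrict the claim of sufficient power to the time and interaction tests.
2. State that between-group power with 64 complete dyads is below the planned 0.80: 0.71 if all four waves are complete, about 0.66 with three.
3. State the number of waves assumed, give the number of dyads with 3-month data, and recompute accordingly.
4. Note that these are complete-case figures, and that a mixed model using partial data from the 103, 90 and 64 dyads could have higher power if dropout is ignorable.
5. Interpret between-group results from the 95% confidence intervals that the Statistical Analysis section already plans, not from post hoc power.

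The cost is a few sentences, one count from the existing data and one recalculation. No new data are needed, and one stated property becomes less favourable.

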## Methods

### Study Design

The proposed project will conduct a randomized controlled trial to assess the effects of the intergenerational reminiscence approach with DST on the social and emotional well-being of older adults with ADRD. An explanatory sequential mixed methods design [39] will be used, which first involves collecting quantitative data and analyzing the data to identify subsamples of participants who report the greatest and least changes and then conducting qualitative interview with these subsamples. Half (46/92, 50%) of the dyad sample will receive the reminiscence DST intervention, and the other half (46/92, 50%) of the sample will receive a regular social visit from young adult volunteers without the intervention. Dyads will be randomly assigned to either the intervention or control group after baseline screening of all participants and, subsequently, randomly matched within each group. To further prevent selection bias, statistical techniques such as covariate-adjusted linear mixed models will be used to adjust for covariate imbalance during data analysis.

A total of 92 dyads are required to test the effectiveness of the intervention in this proposed study (refer to power analysis in the *Sample and Recruitment Plan* section). We will recruit participants on a rolling basis until we recruit 92 dyads. At least one-fourth (23/92, 25%) of the total sample of older adults and young adult volunteers will be recruited before they are randomly matched. Upon signing the consent form, participants will be given the chance to engage in the study. They will be provided with guidance throughout the informed consent process and will subsequently undergo a baseline survey in which all measures will be collected blind to group conditions.

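### The 0.95 interaction power at 64 dyads is not power for a small effect: in that test f=0.22 stands for a between-arm difference of about 0.9 to 1.25 SD

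*Protocol article*

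**What the plan says.** In the Results section the article reports that 92 dyads were planned and 64 completed the posttest survey. It then defends the smaller number with a post hoc G*Power calculation: "64 dyads will yield sufficient power to test the interaction between groups over time (power=0.95"), followed by "the changes over time (power=0.95), and the differences between the groups (power=0.71"). The basis is given as "These parameters are based on a small anticipated effect size" (f=0.22), with "α=0.05, two-tailed, with measures correlated at r=0.30".

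Sampling and Recruitment Plan uses the same f and the same label for the planned 92 dyads: "This sample size estimate was based on a small effect size". That section does not say which test was sized.

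Two design facts fix the calculation. There are four measurements (Data Collection Plan: "Data will be collected at baseline, midpoint, end of the intervention, and 3 months after the intervention by telephone"), and the two arms are of equal planned size (Study Design: "Half (46/92, 50%) of the dyad sample will receive the reminiscence DST intervention"). Statistical Analysis treats the scores at all four waves, baseline included, as the dependent variable of a linear mixed model, and uses a significant interaction to identify different patterns of change in the groups. Nowhere does the article translate f=0.22 into a difference between arms, either in SD units or on an outcome scale.

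**The concern.** One value of f serves three tests, but f measures a different thing in each. For the group test it reflects the average gap between the arms. For the interaction it reflects how much that gap varies from wave to wave. A steady treatment effect that appears after baseline produces only modest variation across waves, so a given f demands a much larger treatment effect in the interaction test than in the group test.

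This matters because baseline is one of the modelled waves. Under randomisation the expected baseline gap is zero, so a treatment effect shows itself as group-by-time interaction. The 0.95 is the more favourable of the two between-arm figures offered for calling 64 dyads sufficient. If it is not power for a small effect, it does not support that conclusion for small or moderate benefits, and it affects how a non-significant interaction may be read in the results papers still to come.

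**Working it through.** **Inputs.** From Results: N=64, f=0.22, r=0.30, α=0.05. From Data Collection Plan: m=4 waves. From Study Design: two arms, taken as equal (32 per arm). Assumed: sphericity, and G*Power's default definition of f.

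**1. Reproducing the stated power.**
- Interaction and time: λ = f²·N·m/(1−r) = 0.0484 × 64 × 4 / 0.70 = 17.70, with 3 and 186 df. Power 0.952; stated 0.95.
- Between groups: λ = f²·N·m/[1+(m−1)r] = 0.0484 × 64 × 4 / 1.90 = 6.52, with 1 and 62 df. Power 0.710; stated 0.71.

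All three figures match. Alternatives do not: three waves give 0.907 and 0.660, two waves give 0.834 and 0.575, and the other G*Power effect-size option (as in SPSS) gives about 0.70 to 0.72 for the interaction. So the meaning of f in the article's calculation is known.

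**2. What f=0.22 means in each test.** Let d_t be the between-arm difference at wave t in outcome SDs.
- Between groups: f = mean(d_t)/2, so the mean difference over waves is 2 × 0.22 = 0.44 SD.
- Interaction: f = SD over waves of d_t, divided by 2, so that SD must be 0.44.

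With d=0 at baseline, later differences in one direction, and D the largest difference:

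| Pattern over the four waves | SD of pattern | D for f=0.22 (0.44/SD) | D detectable at 80% power |
|---|---|---|---|
| 0, 0, D, D | 0.500 | 0.88 | 0.70 |
| 0, D, D, D | 0.433 | 1.02 | 0.81 |
| 0, D/2, D, D | 0.415 | 1.06 | 0.84 |
| linear rise to D | 0.373 | 1.18 | 0.94 |
| 0, D/2, D, D/2 | 0.354 | 1.25 (1.245) | 0.99 |

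The first row is the smallest possible: four values between 0 and D cannot have an SD above D/2. The last column uses the f that gives 80% power at N=64, which is 0.1745, so D = 0.349/SD.

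**3. Interaction power at 64 dyads for smaller effects, pattern 0, D, D, D.** Here f = 0.2165·D.
- D=0.20: f=0.043, λ=0.69, power 0.09
- D=0.44: f=0.095, λ=3.32, power 0.30
- D=0.50: f=0.108, λ=4.29, power 0.375
- D=0.80: f=0.173, λ=10.97, power 0.79

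A simulation with 32 per arm and r=0.30 gave 0.947 at D=1.016, 0.29 at D=0.44 and 0.10 at D=0.20. If small is read as f=0.10 (an assumption, since the article gives no benchmark), interaction power is 0.32.

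**4. Which test the planned 92 fits.** At f=0.22, r=0.30 and 80% power, the interaction needs 42, 48 or 60 dyads with four, three or two waves. The between-groups test needs 80, 90 or 108. Dividing by 0.95 for attrition makes the latter 85, 95 or 114. The planned 92 is not matched exactly, but it lies near the between-groups requirement and well above that for the interaction.

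**5. Sensitivity.** The Results mention 27 intervention dyads; a 27 to 37 split raises 1.02 only to about 1.03 SD. The 64 dyads are those who completed the third survey; with three waves the interaction power is 0.91 and D is 0.93 to 1.08 SD.

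**The case against.** The strongest reply is that nothing is miscalculated and nothing is hidden: f is printed beside the word small, and the less favourable 0.71 stands next to the 0.95. That is correct, and the 0.95 should stay. But the sentence makes a claim about the size of effect the study can find, and by the article's own parameters that size is close to one SD.

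A second reply is that the time pattern is not stated, so no single conversion is justified. This also stands, which is why a range is given. Its floor, with equal baselines and effects in one direction, is still 0.88 SD.

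Third, the interaction test is not the only comparison. Statistical Analysis also plans a 95% CI for each adjusted mean difference. For a sustained effect at 64 dyads and r=0.30, a one-df contrast would detect about 0.69 SD (mean post-baseline change) or 0.47 SD (if adjusted for baseline, although the article lists baseline among the dependent scores). A reader might therefore infer from the interaction figures that the whole trial can detect nothing below 0.8 SD. The article does not support that: 0.81 SD belongs to the three-df test under one pattern. Power at 0.20 SD nevertheless stays low, at 0.13 to 0.22, under either contrast.

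A reader might also carry the one-SD figure back to the planned 92 dyads. That too is unsupported, because the sample size section names no interaction test and its number lies nearer the between-groups requirement, where f=0.22 is 0.44 SD.

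Finally, the article calls the study preliminary and a pilot, and nowhere says that a null interaction excludes a small benefit. True; but the preliminary status is invoked in Statistical Analysis for the multiplicity decision, while the Results still claim sufficient power.

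**Conclusion.** The point holds for the interaction power in the Results. The 0.95 is correctly computed, but it is power for a between-arm difference of about 0.9 to 1.25 SD (1.02 SD if constant after baseline), not for a small effect. For a sustained difference of 0.20 to 0.50 SD the same test has power of about 0.09 to 0.38. These figures rest on G*Power's default definition of f, which the match on all three stated powers supports, and on four waves, equal baselines, r=0.30, sphericity and effects in one direction. In Sampling and Recruitment Plan the fault is limited to calling f=0.22 small without saying what it means for the test that was sized. Data collection is over, so the design cannot change; what changes is what a non-significant interaction can be said to show.

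**What to change.** In Results:
- Remove the word small and the unqualified statement that power is sufficient.
- Keep 0.95, and state the difference it corresponds to: 1.02 SD if constant after baseline, about 0.9 to 1.25 SD across patterns. State beside the 0.71 that there f=0.22 means 0.44 SD averaged over waves.
- Add the difference detectable with 80% power by the overall interaction test at 64 dyads: 0.81 SD if constant after baseline, about 0.7 to 1.0 SD across patterns.
- Say that a non-significant interaction does not rule out small or moderate effects, and refer readers to the planned confidence intervals.

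In Sampling and Recruitment Plan, name the test that was sized and replace the word small with the effect in SD units (0.44 SD averaged over waves if it was the between-groups test). Do not use the one-SD figure there.

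The cost is a few sentences and one calculation, and a less favourable account of what 64 dyads can show.
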